### 11.2.1 Algorithm for DSA response

[figure not shown]

## 12. Management of adverse events

### 12.1 Adverse Events definitions

An Adverse Event (AE) will be defined as any unfavorable and unintended sign, symptom, or disease that occurs during the study, or is present at baseline and significantly worsens following the start of MSCs Infusion or any study procedure. Any AE that occurs prior to the first MSCs infusion will be considered part of the subject's medical history. AEs may include abnormal laboratory findings or other abnormal assessments (e.g., laboratory screening, vital signs, etc.). Accidental traumas are not considered SAEs but the medical condition resulting from the trauma may be an AE or SAE (e.g., a fracture resulting from a fall).

### 12.2 Serious Adverse Events (SAEs)

All serious adverse events (SAE) will be reported to the PI or the study coordinator. An SAE is any untoward medical occurrence that:

- a. Results in death.
- b. Is life-threatening: referring to an event in which the subject was at risk of death at the time of the event. It does not refer to an event, which hypothetically might have caused death if it were more severe or left untreated.
- c. Requires hospitalization or prolongation of existing hospitalization. NOTE: Hospitalization describes an admission for > 24 hours. Over-night stays for observation or stays at the emergency room do not constitute hospitalization. However, the medical judgment must always be exercised and, when in doubt, should be considered an SAE. Any medical/surgical complications which prolong the hospitalization are SAEs. Hospitalization for elective treatment or for a pre-existing condition that did not worsen from baseline is not considered an AE.
- d. Results in disability/incapacity. NOTE: The Investigator must determine that the disability is not related to the expected progression of the patient Parkinson's disease. Also, the term disability means a substantial disruption of a person's ability to conduct normal life functions. This definition is not intended to include experiences of relatively minor medical significance such as uncomplicated headache, nausea, vomiting, diarrhea, and infections which may temporarily interfere or prevent everyday life functions but do not constitute a substantial disruption.
- e. AEs that occur in a higher frequency than can be expected in the PD population.
- f. Any event that the Primary Investigator judges to be an SAE.

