| STUDY DESIGN               | Phase IIa double-blind, randomized controlled trial of allogeneic bone marrow-derived MSCs as a disease-modifying therapy for PD. The study design includes 3 treatment arms: a) 2 infusions of $10 \times 10^6$ MSC/kg and 1 placebo every 4 months; b) 3 infusions of $10 \times 10^6$ MSC/kg every 4 months; c) 3 infusions of placebo every 4 months. All subjects receive 3 infusions, at 4 month intervals, and followed for 88 weeks.                        |

|                                           |                                                                                                                                                                                                                                                                                                                                     |
|-------------------------------------------|-------------------------------------------------------------------------------------------------------------------------------------------------------------------------------------------------------------------------------------------------------------------------------------------------------------------------------------|
| MAIN INCLUSION/ EXCLUSION CRITERIA | 
Inclusion Criteria
 
Men and women between the ages of 50 and 79; DOD 4 to 10 years; UK Brain Bank PD diagnosis, mild microsmia or anosmia, and robust response to dopaminergic therapy.
 
Exclusion criteria
 
Atypical, vascular, or drug-induced Parkinsonism. A MoCA score of less than 25.
 |
| DOSAGE:                            | Intravenous infusion of either placebo or $10 \times 10^6$ MSC /kg of body weight.                                                                                                                                                                                                                                                  |
| DOSAGE: JUSTIFICATION              | Available literature reported safety data and efficacy on dosages ranging from $1-150 \times 10^6$ MSC/kg for other pathologies. Preliminary findings from our Phase I trial showed $10 \times 10^6$ MSC/kg has the largest effect on reducing motor symptoms and improving quality of life.                                        |

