#### 5.1.2 Secondary outcomes

Assess 1) safety and tolerability; 2) secondary measurements of clinical efficacy and 3) explore putative mechanisms of action for the effect of MSC

1. MSC therapy will demonstrate safety and tolerability comparable to placebo in terms of serious adverse reactions and immunologic responses.

- New-onset organ failure defined as a significant acute change in the kidney or liver function, leukocytosis, leukopenia or anemia sustained over 3 months; > 75 % reduction in GFR compared to baseline; altered liver function as defined by ALT >150 U/L and or total bilirubin >1.6 mg/dl; or leukopenia defined as < 4K WBC count or anemia as defined by Hgb < 12 for men and < 11 for women.
  - Immunologic responses: Donor specific antibodies (DSA) in serum of patients will be measured and compared to baseline to determine if there is a development of antibody response to donor HLA. (Please refer to section 11.2)
2. MSC therapy will improve motor function, disability, quality of life, non-motor symptoms, cognition, and behavioral changes relative to placebo.
- Motor function: characterized by a change in MDS-UPDRS Total and Motor scores and Timed-Up-and-Go (TUG) from baseline. Immediate response will be assessed at weeks 29, 39, 52, and 78. Normal progression in UPDRS-T is defined by > 8-14 points per year Therefore abnormal clinical deterioration is an increase of >12 points per year in the “Off” state. For the UPDRS-M, the literature supports a natural progression of 3-6 points per year and this equivalent for the MDS-UPDRS motor section; therefore, abnormal clinical deterioration is an increase of > 6 points per year. TUG progression is defined as a +/- 3 seconds difference every 6 months.
  - Global measurement of disability as measured by the change in the screening “Off” modified Hoehn and Yahr (H&Y) at the final visit. Expected progression is defined as a < 1.0 increase in H&Y every 2 years. Therefore, clinically significant deterioration would be > 0.5 increase in the H&Y over 1-year.

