## 6.5 Method of Assigning Subjects to Study Drug

Subjects will be assigned to any of the three treatment arms randomly on ratio 1:1:1 by computer table randomization method to yield a total of up to 45 randomized treated subjects; 15 subjects per arm. Screen failures or subjects who exit the study prior to the administration of the first treatment dose may be replaced with additional subjects, which could cause an overall number of subjects randomized to be greater than the 45 anticipated. However, no more than 45 subjects will be treated.

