## 8.8 Lumbar Puncture

The same biological markers, as proposed in the peripheral markers, will be assessed in the spinal fluid at baseline and week 49. A qualified neurologist will perform a bedside lumbar puncture under sterile procedural guidelines; approximately 15-20 ccs of CSF will be collected and will take approximately 30-60 minutes. Afterward, the subject will remain recumbent and in observation at the clinical research unit (Part of the Memorial Hermann hospital) for 2 hours following the procedure, with fluid intake encouraged.

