## 9. Potential Risks:

Lumbar puncture: There is some discomfort during the lumbar puncture procedure. After a brief sting from the numbing medication, the subject will feel mostly pressure or occasionally tingling sensations. The most common side effects of a lumbar puncture are headache, nausea, vomiting, or fever. In our experience, approximately 1 % of patients undergoing a lumbar puncture can develop a refractory headache (positional). Most post LP headaches respond to lying flat and resting for 48 hours and drinking plenty of fluids and caffeinated beverages as tolerated. By definition, they are refractory if they fail to resolve after these measures are taken and an autologous blood patch performed by anesthesia or neuroradiology is the treatment of choice for immediate resolution.

Blood draw: Blood draws, and infusions may cause discomfort, pain, and bruises at the site where blood is taken and sometimes causes people to feel lightheaded or to faint.

MRI scanning: All participants will be screened for metallic implants incompatible with the MRI environment. If a patient experiences unbearable claustrophobia inside MRI scanners, he/she will be removed from the scanner.

Cognitive, neurologic, and physical exams and history: These are administered by medical professionals. However, there may be some subjects embarrassed or anxious due to the questions that must be answered.

Acute immune reactions: The PI will ensure that appropriate best clinical practices and treatment are initiated should an event indicating an allergic or hypersensitive reaction occur. If this occurs, the infusion will be stopped immediately, and the subject closely monitored until stable. The suggested treatment will depend upon the grading of the reaction (NCI-CTCAE criteria). The PI will have the support of the emergency response teams from the hospital as needed. After the infusion, patients will be continuously monitored for 4 more hours, and a full neurological physical examination will be performed before discharging the patients. In case of a severe adverse event,

we can get an assessment in regards to the continuation of the study from our DSMB within 24-48 hours.

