#### Mandatory Unscheduled DSMB Review:

Study suspension is defined as a hold on recruitment. The following criteria require a review and a recommendation from the DSMB for continuation, suspension or termination of the study:

- Unexpected significant worsening of functional motor state as documented by a change at 6 months in: the MDS-UPDRS total score of > 10 points or > 5 points for the motor MDS-UPDRS subscale or an increase in H&Y of 1 or more.
- An SAE related or possibly-related to the infusion, occurring at any time post-dosing
- 2 possibly-related or related, unexpected, Grade 3 or higher Infusion-Related Allergic Reactions observed per 3 treated subjects at any time post-infusion.

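### Section 12.2 item (e) uses a group-level frequency, with no stated rate, margin or severity condition, to decide whether a single patient's event is serious

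*Protocol*

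**What the plan says.** Protocol section 12.2 defines an SAE as an occurrence meeting any of items (a) to (f). Items (a) to (d) are death, threat to life, hospitalization and disability. Item (f) is the investigator's judgment. Item (e) is "AEs that occur in a higher frequency than can be expected in the PD population". A note under (d) keeps minor complaints, such as uncomplicated headache, nausea, vomiting, diarrhea and infections, out of the disability criterion. Item (e) has no such note.

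The definition is operative. Section 12.4 has the investigator record for each AE its CTCAE severity grade (item 1) and, separately, whether it is serious as defined in section 12.2 (item 7).

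Several provisions depend on that label:
- Section 16 requires DSMB notice within 24 hours of an SAE.
- Section 16 also lists, among the triggers for a mandatory unscheduled review, "An SAE related or possibly-related to the infusion, occurring at any time post-dosing".
- Section 5.1.2 sets the safety outcome: "MSC therapy will demonstrate safety and tolerability comparable to placebo in terms of serious adverse reactions and immunologic responses". Section 14.3, Hypothesis 2.1, models serious adverse reactions.

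The study procedures are common to all arms. The synopsis states "All subjects receive 3 infusions, at 4 month intervals, and followed for 88 weeks", and section 8.8 says that CSF markers "will be assessed in the spinal fluid at baseline and week 49".

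**The concern.** Items (a) to (d) can be judged from one patient's record. Item (e) cannot, because a single event has no frequency. To apply it, an investigator needs an expected rate, a counting unit (patients or events), a window and a size of excess, and the protocol supplies none of these. Two investigators could not be expected to apply it alike. Site personnel are blinded (section 14.1), so whoever applies it sees only pooled frequencies and cannot use the trial's own placebo arm.

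Item (e) also ignores severity, although section 12.4 separates severity from seriousness. Section 12.1 allows abnormal laboratory findings to count as AEs, so mild laboratory shifts are within reach of (e) as well.

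At stake is what an SAE means in this trial. If minor events can carry the label, some expedited notices and mandatory reviews will concern events that are not serious in the sense of (a) to (d), and the serious-reaction comparison will include them.

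**Working it through.** The protocol gives no rate, threshold or error probability for item (e), so there is no figure of its own to reproduce. Two separate mechanisms can make a minor event serious.

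**Inputs.** Section 6.5: "total of up to 45 randomized treated subjects; 15 subjects per arm". Three infusions per subject in every arm (synopsis). Punctures at baseline and week 49 (section 8.8). Phase I (section 3.5): one phlebitis and one hematoma among 20 patients, 1/20 = 5% each, both rated related to the cells. The hematoma was mild and untreated. The phlebitis was Grade 2 and managed locally. As described, neither meets (a) to (d).

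**1. Background near zero.** If the PD population means patients who have no study infusion, an infusion-site hematoma or phlebitis has an expected rate near zero, and the first case exceeds it. With a true rate r per subject, P(at least one case in m subjects) = 1 − (1 − r)^m. Taking r = 5% from Phase I as an illustration:
- whole trial, m = 45: 1 − 0.95^45 = 0.90
- one arm, m = 15: 1 − 0.95^15 = 0.54

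This applies to placebo as well, since placebo subjects are also cannulated three times.

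Lumbar-puncture events are a narrower case. Section 9 says "The most common side effects of a lumbar puncture are headache, nausea, vomiting, or fever". Section 12.1 treats anything before the first infusion as medical history, and section 12.4 starts AE documentation at visit 3. The baseline puncture (visit 2) therefore drops out and only week 49 remains. Headache and nausea in general also have a non-zero background in PD, so they are not caught at the first case.

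**2. No true excess.** Read item (e) literally as observed frequency above the expected rate p0. For X ~ Binomial(n, p0), the probability that one event type meets it by chance is P(X ≥ floor(n·p0) + 1). The rates are assumptions.

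| Assumed p0 | n = 45: cases needed | n = 45: probability | n = 15: cases needed | n = 15: probability |
|---|---|---|---|---|
| 0.5% | 1 | 20% | 1 | 7% |
| 1% | 1 | 36% | 1 | 14% |
| 2% | 1 | 60% | 1 | 26% |
| 5% | 3 | 39% | 1 | 54% |
| 10% | 5 | 47% | 2 | 45% |
| 20% | 10 | 41% | 4 | 35% |
| 30% | 14 | 49% | 5 | 48% |
| 50% | 23 | 50% | 8 | 50% |

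Over p0 from 5% to 50% in steps of 0.5 points, the range is 38-57% for n = 45 and 28-64% for n = 15. The values move up and down because counts are whole numbers.

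**3. Would a bare comparison with placebo do better?** With 15 per arm and the same true rate everywhere, the probability that at least one active arm has more cases than placebo is 1 − Σ f(k)·F(k)², where f and F are the Binomial(15, q) mass and distribution functions. This gives 49% at q = 5%, 54% at 10% and 57% at 20%. Moving the comparison to the DSMB without a threshold would remove the SAE label but leave an equally noisy signal.

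**The case against.** The strongest reply is that the chance figures are not properties of the protocol. No section prescribes a running tally or a numerical test. Higher than expected can be read as more than chance would explain, and section 12.4 leaves identification to the investigator's judgment. This stands: the probabilities describe one literal reading with assumed rates. It does not rescue the item, since that judgment has no rate, window or margin to work from.

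A reader might infer that the rule fires about half the time with no excess, or almost always once several event types are watched. The documents do not support either as a general statement. For rare types the probability is well below half (20-36% in 45 patients at rates of 0.5-1%). A figure for several types needs independence, and section 9 lists headache, nausea, vomiting and fever together as effects of one procedure.

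A reader might also infer that lumbar-puncture events become SAEs and set off mandatory reviews. Baseline-puncture events are excluded. The week-49 puncture comes 13 weeks after the last infusion at week 36, so a headache after it would not naturally be judged infusion-related, as the section 16 trigger requires.

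On the safety outcome, section 5.1.2 refers to serious adverse reactions, so unrelated procedural SAEs need not enter it. Extra events falling equally on all arms leave the expected absolute difference unchanged and add variance. CTCAE grades are recorded, so mild events remain separable in analysis. Mild Phase I laboratory findings (decreased lymphocytes 6/20, increased basophils 4/20) would qualify only if their PD background were below 30% and 20%, which is not stated.

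Finally, a wide net is defensible in a first repeat-dose study. That aim is reasonable, but it is an aggregate one, and section 16 already has the DSMB reviewing aggregate data after infusions.

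**Conclusion.** The concern holds in a limited form. Item (e) is a group-level frequency statement placed in a case-level definition. It cannot be applied consistently as written, and it bypasses the minor-event note under (d). Because section 12.4 makes it operative, minor procedure-specific events such as infusion-site hematoma or phlebitis can become SAEs in any arm, provided the comparator is PD patients without infusions. The consequences are 24-hour DSMB notice, mandatory review where the event is judged related or possibly related to the infusion, and non-serious events in the serious-reaction comparison.

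The size is conditional. Under the literal reading with no true excess, one event type in 45 patients meets the criterion with probability about 38-57% for background rates of 5-50% and 20-36% for rates of 0.5-1%. It reaches 60% at 2%, where a single case suffices. All of these rates are assumed. This should be corrected, but it does not undermine the design.

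**What to change.** Remove item (e) from the section 12.2 definition and keep (a) to (d) and (f). Add an aggregate item to section 16: at its scheduled reviews the DSMB examines AE frequencies by type and arm, comparing each active arm with concurrent placebo. State a margin or posterior-probability threshold in advance, so that a numerical excess alone is not a signal; the latter fits the Bayesian framework of section 14.

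As an illustration of what a threshold achieves, suppose an external background rate were adopted with an exact one-sided 5% binomial limit. In one arm of 15 it would require at least 3, 5 or 7 patients at rates of 5%, 10% or 20%, with false-signal probabilities of 3.6%, 1.3% and 1.8%. In all 45 it would require 6, 9 or 15 patients, with probabilities of 2.4%, 3.2% and 2.5%.

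The cost is a short amendment and matching case report form guidance. The downside is that slightly fewer events receive expedited DSMB notice. The investigator can still call any event serious under (f).

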### 12.3 AE Relationship

- Definitely related: symptoms experienced a temporal sequence from MSC administration or discontinuance.
- Probably related: symptoms experienced a temporal sequence from MSC administration or discontinuance and cannot be reasonably explained by another known clinical condition.
- Possibly related: symptoms experienced a temporal sequence from MSC administration or discontinuance but could have been produced by another known clinical condition or by other therapies administered to the subject.
- Unlikely related: The temporal sequence between the AE/SAE and the MSC administration is such that the infusion is not likely to have had any reasonable association with the symptoms, and the AE/SAE could have been produced by another known clinical condition or by other therapies administered to the subject.
- Unrelated: The AE/SAE is definitely produced by another known clinical condition or by other therapies administered to the subject, and the AE does not follow a temporal sequence from MSC administration or discontinuance.

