There was no response to donor HLA over the 12-month study. At 52 weeks CCL2 declined by 15% ( $p<0.01$ ), and CCL22 by 29% ( $p<0.05$ ), along with an increase in BDNF 46% ( $p<0.05$ ). The highest dose had the most significant effect on reducing OFF UPDRS motor -14.4 ( $p<0.01$ ) and total scores (-20.8,  $p<0.001$ ). Further, there was an increase in basal ganglia perfusion at 24 weeks ( $p<0.001$ ).

| Body System      | Adverse Reaction          | Group A
N=5
(100%) | Group B
N=5
(100%) | Group C
N=5
(100%) | Group D
N=5
(100%) | AE Relationship to MSC |
|------------------|---------------------------|--------------------------|--------------------------|--------------------------|--------------------------|------------------------|
| Cardiovascular   | Hypertension              | 2 (40%)                  | 2 (40%)                  | 0                        | 0                        | Unlikely related       |
|                  | Phlebitis b    | 0                        | 0                        | 0                        | 1 (20%)                  | Related                |
|                  | Hematoma b     | 0                        | 0                        | 1 (20%)                  | 0                        | Related                |
| Gastrointestinal | Nausea a       | 1 (20%)                  | 2 (40%)                  | 0                        | 0                        | Possibly related       |
| Neurologic       | Headache b     | 0                        | 1 (20%)                  | 0                        | 0                        | Possibly related       |
|                  | Dyskinesia                | 1 (20%)                  | 0                        | 2 (40%)                  | 1 (20%)                  | Probably related       |
| Hematology       | CLL                       | 0                        | 0                        | 1 (20%)                  | 0                        | Possibly related       |
| Lab              | ↓Lymphocytes a | 3 (60%)                  | 2 (40%)                  | 0                        | 1 (20%)                  | Possibly related       |
|                  | ↑Basophils a   | 1 (20%)                  | 1 (20%)                  | 1 (20%)                  | 1 (20%)                  | Possibly related       |

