### 12.4 AE/SAE Reporting

AE/SAE will be documented at each clinic visit starting at visit 3. Information on adverse effects will be determined at each clinic visit by direct questioning of the subjects, vital signs, clinical assessment, laboratory test, and by interval telephone evaluations starting 1 week after the first infusion using a set of questions to identify symptoms or signs related to an adverse event and will continue through the rest of the study.

The PI, with the assistance of her study team, will be responsible for the detection and documentation of events meeting the criteria and definition of an AE or SAE as provided in this protocol. For each AE and SAE, the PI will make an assessment of:

1. The severity grade (CTCAE criteria).
2. The duration (start and end dates or if continuing at the Safety Follow-up Visit).
3. Its relationship to the study treatment (Reasonable possibility that AE is related: No, Yes).  
The investigator will use clinical judgment to determine the relationship, alternative causes (e.g. the natural history of an underlying disease, concomitant therapy, other risk factors), and the temporal relationship of the AE to the infusion procedure will be considered and investigated.
4. Action taken with respect to study or investigational treatment (none, dose adjusted, temporarily interrupted, permanently discontinued, hospitalized, unknown, not applicable).
5. Whether medication or therapy was given (no concomitant medication/non-drug therapy, concomitant medication/non-drug therapy).

6. Outcome (not recovered/not resolved, recovered/resolved, recovering/resolving, recovered/resolved with sequelae, fatal, unknown).
7. Whether it is serious, where a serious adverse event (SAE) is defined as in Section 12.2.

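### Section 12.3 sets a weaker test for *Definitely related* than for *Probably related*, so the top three causality grades overlap, and the No/Yes item in section 12.4 is not linked to them

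*Protocol*

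**What the plan says.** Protocol section 12.3 (AE Relationship) lists five grades.

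- Top grade, in full: "Definitely related: symptoms experienced a temporal sequence from MSC administration or discontinuance".
- *Probably related*: the same timing condition, "and cannot be reasonably explained by another known clinical condition".
- *Possibly related*: the same timing condition, "but could have been produced by another known clinical condition or by other therapies administered to the subject".
- *Unlikely related*: the timing "is such that the infusion is not likely to have had any reasonable association with the symptoms", and another cause could have produced the event.
- *Unrelated*: definitely due to another cause, and no temporal sequence.

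Section 12.4 (AE/SAE Reporting) then asks the investigator to record, for each event, "Its relationship to the study treatment (Reasonable possibility that AE is related: No, Yes". This is to be decided by clinical judgment, with alternative causes and timing considered. The five grades are not mentioned there.

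The SUSAR rule in 12.4 covers events related or possibly related to the study drug or to taking part in the research. Section 16 requires an unscheduled DSMB review for "An SAE related or possibly-related to the infusion, occurring at any time post-dosing".

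Section 5.1.2 makes safety comparable to placebo, in terms of serious adverse reactions and immunologic responses, the first secondary outcome. Hypothesis 2.1 in section 14.3 models serious adverse reactions by arm.

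**The concern.** In a graded causality scale, each step up should ask for more evidence. Here the top step asks for less than the one below it. An event with a clear alternative explanation fits *Possibly* and, on the wording, also fits *Definitely*. Two raters who both follow the text can therefore give the same event different grades, and neither is wrong.

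Relatedness is what turns an adverse event into an adverse reaction. Serious adverse reactions are a named safety comparison with placebo, and safety is part of the primary objective of choosing the number of doses. If raters follow the text, the top grade does not separate an infusion reaction from a coincidental event. If they follow their own idea of what is definite, the recorded grades no longer match the written definition. The unlinked No/Yes item adds a second answer to the same question, with no rule for what happens when the two disagree.

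**Working it through.** No figure is stated in the plan on this point, so the check is logical.

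**Inputs (section 12.3).** Let T = the event follows a temporal sequence from administration or discontinuance; C = another known clinical condition reasonably explains it; R = another therapy could have produced it.

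**Definitions as worded.**
- *Definitely* = T
- *Probably* = T and not C
- *Possibly* = T and (C or R)

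**All combinations with T present.**

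| C | R | Definitely | Probably | Possibly |
|---|---|---|---|---|
| no | no | meets | meets | – |
| no | yes | meets | meets | meets |
| yes | no | meets | – | meets |
| yes | yes | meets | – | meets |

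Every row meets *Definitely*, and every row meets at least one of the other two. *Definitely* is therefore exactly the union of *Probably* and *Possibly*. No row belongs to one grade only. In the second row all three apply, because *Probably* rules out other conditions but not other therapies.

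**Is the whole scale reversed?** No. From *Probably* through *Possibly* and *Unlikely* to *Unrelated*, the evidence for a link falls at each step. Only the top grade is out of place.

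**Do the pooled triggers move?** Take related to mean *Definitely* or *Probably*; the document does not say so. The SUSAR and DSMB rules then use *Definitely* or *Probably* or *Possibly*. From the table, that set equals T whichever of the three grades a rater picks, so both triggers are unchanged.

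**How many events are affected?** Section 12.3 gives no time window for T. Section 12.1 counts as adverse events only those after the first infusion, so literally every recorded event follows an infusion. The definition of *Unlikely*, however, implies that timing has to be plausible. Under assumed windows after each of the three infusions (weeks 0, 18 and 36, followed to week 88), the part of follow-up covered is:
- 4 weeks: 3 × 4 = 12; 12/88 = 14%
- 18 weeks: 3 × 18 = 54; 54/88 = 61%
- no window: 88/88 = 100%

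These are shares of follow-up time under assumptions, not shares of events. The document gives no basis for choosing among them or for turning them into event counts.

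**Sections 12.3 and 12.4 side by side.** The first yields five grades, the second No or Yes. No sentence says which grades count as Yes, or which of the two fields feeds the SUSAR rule, the DSMB rule or the serious adverse reactions analysis.

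**The case against.** The strongest reply is that no rater reads the first bullet alone. An event with another possible cause has its own grade, *Possibly*. Implausible timing has *Unlikely*. Section 12.4 tells the investigator to use clinical judgment and to weigh alternative causes. This stands as a limit on the practical effect. It does not repair a definition that asks for timing only.

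It is also fair that much of the safety assessment does not depend on this scale. The organ-function and donor-antibody elements of 5.1.2 rest on laboratory criteria, the primary outcome is judged on the motor score, and the pooled triggers do not move. A randomised comparison that pools all three top grades is unaffected as well. The missing link to No/Yes is minor on its own: a reasonable possibility pairs naturally with the top three grades, and such a mapping often sits in the CRF.

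A reader might infer three stronger things that the document does not support.

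- *Nearly every post-infusion event would be graded definitely related.* This holds only if the bullet is read without the rest of the list and without 12.4.
- *Placebo events being graded as readily as MSC events is itself a defect.* Site personnel are blinded (14.1), and equal grading across arms is what blinding should produce. Read literally, a placebo recipient has no MSC administration at all. That is a reason to change the term, not evidence of bias.
- *The Phase I table in section 3.5 gives the size.* Its column "AE Relationship to MSC" covers 25 patient-level entries: 2 related, 4 probably, 15 possibly and 4 unlikely. Applying the 12.3 wording would put 2 + 4 + 15 = 21 of 25 (84%) in the top grade instead of 2 of 25 (8%). The count is right, but the inference is not. That was a separate open-label study, its causality definitions are not shown, and its top label is not the one used here. If it did use this wording, its raters evidently did not apply it literally.

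**Conclusion.** The definition is wrong as written. *Definitely related* has a weaker condition than *Probably related*, and the top three grades overlap in every combination of alternative causes. Sections 12.3 and 12.4 also hold two relatedness records with no stated link.

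The consequence is limited to the relatedness grading behind the serious adverse reactions comparison (5.1.2, Hypothesis 2.1), and to any table that separates definite from probable or possible. It would change counts if an analysis set its threshold above *Possibly*; it would not if all three top grades are pooled. The statement that the SUSAR and DSMB triggers are unaffected assumes that related there means *Definitely* or *Probably*. The number of events affected cannot be derived from the document.

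**What to change.** In section 12.3:

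- Give *Definitely related* at least the *Probably* condition (plausible timing and no other clinical condition as a reasonable explanation), plus exclusion of other therapies and one further criterion beyond timing that a blinded rater can apply. A list of event types fixed in advance is one example; the choice is for the investigators.
- Do not use recurrence at the next infusion as that criterion. Section 11.1 discontinues study treatment after Grade 3 or 4 infusion reactions, so recurrence often cannot be observed. One active arm has a placebo infusion among its three, so a blinded rater could not interpret recurrence or its absence.
- Make the grades mutually exclusive. One way is for *Probably* also to exclude other therapies. An event with plausible timing and any alternative cause is then *Possibly*. One with no alternative cause is *Definitely* if the further criterion is met and *Probably* if not.
- Refer to the study infusion instead of MSC administration, so that the wording applies in the same way in all three arms.

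In section 12.4, state the mapping: *Definitely*, *Probably* and *Possibly* = Yes; *Unlikely* and *Unrelated* = No.

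The cost is wording in two sections and one CRF field, with no new data or staff. The downside is that events already recorded have to be regraded, which should be done blinded.
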